## Abstract

**Importance:**

Cognitive training with components that can further enhance the transferred and long-term effects and slow the progress of dementia is needed for preventing dementia.

**Objective:**

The goal of the study is to test whether improving autonomic nervous system (ANS) flexibility via a resonance frequency breathing (RFB) training will strengthen the effects of a visual speed of processing (VSOP) cognitive training on cognitive and brain function, and slow the progress of dementia in older adults with mild cognitive impairment (MCI).

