There are several categories of interventions that can explicitly improve ANS flexibility, including physical exercise [12, 13], non-invasive brain stimulation [14–16], and biofeedback intervention [17]. Mechanisms underlying the improvement include modifying the central efficiency of ANS flexibility, stimulating activity of the baroreflex, or regulating dopaminergic and cholinergic transmission [15, 18]. The effect sizes of these interventions on central and peripheral pathways of ANS flexibility vary: so far, the most robust intervention effect is from HRV biofeedback intervention (HRVB). HRVB entails feeding back beat by beat heart rate data during slow breathing maneuvers such that the participant tries to maximize peripheral nervous system function (indexed by high-frequency heart rate variability (HF-HRV)). The key behavioral component of HRVB is resonance frequency (RFB), that is, breathing at a rate which maximizes respiratory sinus arrhythmia (RSA), the synchronization of HR change (increases/decreases) with respiratory (inhalation/exhalation) patterns, creating a sine-wave-like curve of peaks and valleys. Multiple mechanisms are involved in explaining the effects of RFB on ANS, including (1) phase relationships between HR oscillations and breathing at specific frequencies (i.e., maximizing RSA), (2) phase relationships between heart rate and blood pressure oscillations at specific frequencies, (3) activity of the baroreflex, and (4) resonance characteristics of the cardiovascular system, all of which have been previously reviewed comprehensively [19]. Individuals can be easily trained to engage in RFB via an assistive mobile app that guides the individual, with a visual pacer, through a paced breathing exercise. A recent meta-analysis revealed an effect size of Hedges’ *g* = 0.83 for comparing HRVB (ranges 1–50 sessions) to other control interventions on improving adaption to real-world stressors (e.g., perceived stress and anxiety trait and state) [17]. Although RFB has not been tested in groups at risk for dementia, HRVB using RFB training improves resting HRV, executive function, and anxiety in traumatic brain injury [20, 21] and older adults [22]. HRVB also improves HRV response to cognitive stress [23]. We propose that adding RFB to a cognitive training can strengthen the effect on ANS flexibility and overall adaptation capacity, which in turn may directly modify markers of dementia progression, and may also indirectly enhance individuals’ adaptation to cognitive challenges provided by the cognitive training and strengthen cognitive training effect on markers of dementia. Lastly, compared to other intervention strategies for modifying ANS flexibility (e.g., vagal nerve stimulation, exercise, non-invasive brain stimulation), we suspect our proposed intervention approach, due to the minimal side effects, self-administrable nature, and potential effectiveness, may ensure a fast translation into real-world practice.

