
The objective of the study is to test whether adding RFB to the vision-based speed of processing training (VSOP)—the most widely tested cognitive training among older adults [24–27]—will enhance the training effects of VSOP by strengthening adaptation capacity that affords greater adaptive learning and neuroplasticity, and slow the progress of dementia in MCI. We will examine long-term effects of the combined intervention on ANS flexibility and cognitive and functional capacity and explore potential long-term effects of the combined intervention on neurodegeneration. Relevant hypotheses include the following: the combined intervention will have a greater effect on CAN and HRV—indicators of autonomic flexibility—as well as cognition and everyday function, and less neurodegeneration, compared to control groups throughout the follow-up period; improvements in ANS flexibility will predict improvement on cognition and everyday function and slower neurodegeneration over time.

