## Methods

### Trial design

We plan to conduct a double-blinded, phase II randomized controlled trial (RCT). Older adults with MCI (*n* = 114) will be randomly assigned to an 8-week combined intervention (RFB+VSOP), VSOP with imagery-guided relaxation control (IR+VSOP), or a IR-only control, with 2-week booster sessions provided at 3 and 9 months after the intervention. Variables include ANS flexibility measured by central autonomic networks (central pathway) and heart rate variability (HRV; peripheral pathway) at rest and in response to a cognitively challenging task, and multiple markers of dementia progress, including cognition (battery tests of episodic memory and executive function), neuropsychiatric symptoms (NPS), instrumental activities of daily living function (IADL), and neurodegeneration (blood-based Alzheimer’s pathological markers and T1 cortical thickness measure). Data will be collected across a 14-month period: baseline and up to 3 time points after the intervention (immediately, 6 months, and 12 months after the intervention). An overview of the trial design is provided in Table 1.

**Table 1 Tab1:** Overview of the study design

	Enrollment	Allocation	Post-allocation																		Close-out
Timepoint	***-1m***	0	***1m***	***2m***	***3m***	***4m***	***5m***	***6m***	***7m***	***8m***	***9m***	***10m***	***11m***	***12m***	***13m***	***14m***	***15m***	***16m***	***17m***	***18m***	***19m***
**Enrolment**	X																				
**Eligibility screen**	X																				
**Informed consent**	X																				
**Allocation**		X																			

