### Data analysis

#### Determine the intervention effect on outcomes

All primary analyses will follow *the intention-to-treat principle* (e.g., group assignment in the analysis will be based on randomized group assignment regardless of the level of adherence to provide unbiased comparisons of the effects among the groups). This principle will account for any potential data loss. We will fit linear mixed-effect models for each outcome measure, accounting for repeated measures at baseline, post-intervention, and 6- and 12-month follow-up. The models will include fixed effects for data collection visit (categorical variable), group assignment (compare the combined group with other groups), visit and group interaction, respective baseline outcome measure, and covariates identified as being imbalanced among groups. Stepwise variable selection using Akaike Information Criteria will be used to select the fixed effects for inclusion. A random participant-specific effect will be included to account for correlation between visits in the same participant. The model-based average within-group change in outcome measure for each group will be computed at each post-intervention and follow-up point. This will allow us to rank the groups in terms of average within-person gains in each outcome measure. In addition, *the effect sizes of RFB+VSOP and IR+VSOP control for each outcome measure* will also be calculated using standardized mean difference with 95% CI [(*M*_int_ − *M*_control_ at later time) − (*M*_int_ − *M*
_control_ at baseline)]/intra-participant standard deviation; “int” refers to combined intervention or VSOP; “control” here refers to attention control. The effect size of RFB+VSOP will be compared with that of the IR+VSOP control group to determine the additive effect.

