#### Determine the relationships between changes of outcomes

We will first examine correlations between the changes of central and peripheral measures of ANS at rest and reactivity, respectively, from baseline to later time points for the entire sample. Next, we will use the mixed-effect model to determine the main and interaction effects of change in ANS measures (primarily, reactivity) and group on changes of each dementia progress measure (comparing baseline to later time points). Performing this analysis is to determine whether a change in ANS flexibility will lead to greater improvement in dementia progress measures in the combined intervention group, compared to other groups.

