## Discussion

We capitalize on adding RFB practice to VSOP to modify ANS flexibility, which we in turn hypothesize will further strengthen the effect of VSOP on multiple markers of dementia progress. Adaptation capacity to environmental demands contributes to long-term cognitive and functional maintenance in old age regardless of the effect of neurodegeneration. Therefore, enhancing ANS flexibility, essential for adaptation capacity, may impact the long-term cognitive and functional outcomes in old age, including those at risk for dementia. RFB provides a bottom-up modulation that may directly enhance the neurobiological adaptation during VSOP training that is required for neuroplasticity. Further, along with enhanced neuroplasticity and cognitive outcomes, we suggest that combining RFB and VSOP will strengthen overall adaptation capacity better than VSOP alone. Together, these effects are hypothesized to slow dementia progress. Such a combined intervention approach is novel, but grounded in a solid mechanistic understanding.

Our work is inspired by a novel conceptual framework of “physiological geroscience,” which proposes a primary-prevention approach to addressing aging-associated physiological factors that in turn can slow aging and extend the healthspan [68]. Seals et al. suggest that optimizing physiological function via lifestyle interventions, pharmaceuticals, etc., in the aging process can slow down the decline of other interrelated functions (e.g., cognitive function and neurodegeneration) and delay the incidence of aging-associated diseases (e.g., dementia). We are among the first to apply this approach to examine whether modifying ANS flexibility, and therefore increasing adaptation capacity, can slow the progress of dementia. The components of ANS flexibility are vulnerable to aging. Vascular-wise, aging-related decline in endothelial function leads to changes in baroreflexes [69]; neurologically, aging-related decline is implicated in the decreased neural efficiency of central autonomic networks [70]. Both mechanisms can cause the disruption of the ANS flexibility [10, 71], which in turn affects the regulation of self-oriented behaviors, including stress adaptation.

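### The stated objective is that RFB strengthens the effect of VSOP, but the three arms can only show the effect of RFB rather than IR when each is given with VSOP

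*Protocol article*

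**What the plan says.** **Objective.** The Abstract (Objective) says the study tests whether RFB "will strengthen the effects of a visual speed of processing (VSOP) cognitive training on cognitive and brain function". The Introduction's closing paragraph is more specific: it asks whether adding RFB "will enhance the training effects of VSOP by strengthening adaptation capacity that affords greater adaptive learning and neuroplasticity". The Discussion repeats strengthening of VSOP as a hypothesis.

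**Routes.** The Introduction proposes that adding RFB can strengthen autonomic (ANS) flexibility, "which in turn may directly modify markers of dementia progression, and may also indirectly enhance" how participants adapt to the challenges of the training. These are two separate routes to the same outcomes.

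**Arms.** Under Trial design, participants "will be randomly assigned to an 8-week combined intervention (RFB+VSOP), VSOP with imagery-guided relaxation control (IR+VSOP), or a IR-only control". The section on guided imagery relaxation describes IR as matched to RFB practice in dose and frequency and included to control for relaxation effects.

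**Analysis.** Under Data analysis (intervention effect on outcomes), effect sizes for RFB+VSOP and IR+VSOP are each computed against the attention control. Then: "The effect size of RFB+VSOP will be compared with that of the IR+VSOP control group to determine the additive effect". The next subsection relates change in ANS measures to change in dementia markers by group, "to determine whether a change in ANS flexibility will lead to greater improvement in dementia progress measures in the combined intervention group". Under Measures, weekly ECG trajectories are to be related to intervention effects.

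**Discussion.** The authors suggest that "combining RFB and VSOP will strengthen overall adaptation capacity better than VSOP alone".

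**The concern.** To strengthen the training effect of VSOP is a statement about effect modification: VSOP does more when RFB accompanies it than when it does not. To see that, one must know what RFB does without VSOP. No arm shows this. If RFB improves the markers directly, RFB+VSOP will beat IR+VSOP even when VSOP works exactly as it would have done with IR.

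The analysis section calls the contrast additive. On the mean scale of the planned linear models, exact additivity means no interaction, which is the case in which RFB does not strengthen VSOP. Objective and analysis thus use words for different quantities.

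What is at stake is the meaning of a positive result. It would support giving RFB rather than IR with VSOP. It would not tell the next-stage trial that the Discussion foresees whether the gain depends on pairing RFB with VSOP. The reference to VSOP alone adds a smaller problem, because the only comparator without RFB that includes VSOP also includes daily IR.

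**Working it through.** The protocol gives no numerical figure for this question, so there is none to reproduce. The check is one of identification.

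**1. Notation.** Take mean change in each arm on a common SD scale:
- IR only = m
- IR+VSOP = m + v
- RFB+VSOP = m + v + r + s

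Here v is the effect of VSOP given with IR, r is the effect of RFB rather than IR in the absence of VSOP (the direct route), and s is the extra effect of VSOP when RFB replaces IR (strengthening).

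**2. The planned comparison.** I read the attention control as the IR-only arm and assume the same SD divides both effect sizes. Baseline differences have expectation zero under randomisation.
- Effect of RFB+VSOP: (m + v + r + s) − m = v + r + s
- Effect of IR+VSOP: (m + v) − m = v
- Difference: (v + r + s) − v = **r + s**

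The IR-only arm cancels. What remains is RFB+VSOP minus IR+VSOP.

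**3. Can r and s be separated?** In the order m, r, v, s the arm rows are:
- RFB+VSOP: (1, 1, 1, 1)
- IR+VSOP: (1, 0, 1, 0)
- IR only: (1, 0, 0, 0)

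This matrix has rank 3 for 4 parameters. Adding any amount to r and subtracting it from s changes none of the three means. A fourth row for RFB without VSOP, (1, 1, 0, 0), gives rank 4.

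**4. Illustration.** Take m = 0 and v = 0.30 (assumed) and r + s = 0.20, the small effect named under Sample size.

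| r (direct) | s (strengthening) | IR only | IR+VSOP | RFB+VSOP | RFB without VSOP (absent) |
|---|---|---|---|---|---|
| 0.20 | 0 | 0.00 | 0.30 | 0.50 | 0.20 |
| 0 | 0.20 | 0.00 | 0.30 | 0.50 | 0.00 |
| 0.10 | 0.10 | 0.00 | 0.30 | 0.50 | 0.10 |
| 0.40 | −0.20 | 0.00 | 0.30 | 0.50 | 0.40 |

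All four rows give identical expected data in the arms randomised. Only the absent cell differs. Sample size does not enter, so enlarging these arms does not help.

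**5. Do the mechanism analyses help?** ANS change and weekly ECG trajectories arise after randomisation and are not themselves randomised, so their relation to outcome can be confounded. RFB-induced ANS change is also seen only in people receiving VSOP. A steeper slope in the combined arm could reflect ANS change acting directly on the markers or better learning from VSOP.

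**6. VSOP alone.** RFB+VSOP minus VSOP alone equals (r + s) plus the effect of adding IR to VSOP. The trial does not estimate that last term.

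**7. Scale of a fourth arm, for context.** In a 2×2 design with n per cell and one post-treatment measure (assumed), the interaction has variance 4·SD²/n. With two-sided alpha 0.025 (the protocol gives 0.025 but not the sidedness) and 80% power (assumed), the z sum is 2.241 + 0.842 = 3.083.
- Detectable interaction at 32 per cell (96/3): 3.083 × √(4/32) = 1.09 SD
- Detectable interaction at 38 per cell: 3.083 × √(4/38) = 1.00 SD
- Cell size for 0.20 SD: 4 × (3.083/0.20)² ≈ 951
- Power for 0.20 SD at 32 per cell: about 5%

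**The case against.** The algebra is hard to dispute, but the reading of the protocol can be contested.

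- **Strengthen may only mean more benefit when RFB is added.** The protocol never speaks of synergy or an RFB-by-VSOP interaction, and its analysis section says additive. On that reading the planned contrast answers the question. This is fair as a reading of intent, and if it is the intent the rewording costs nothing. It does not fit the Introduction's objective, which places the gain in VSOP's own training effects and sets the direct route apart from the indirect one.
- **The hypotheses are testable.** The Introduction's first hypothesis predicts greater effects in the combined arm than in the control groups. This stands in full: the design tests it, and it needs no change.
- **No conclusion is prespecified.** A reader might infer that the plan commits the sponsor to announcing synergy or superiority to VSOP alone. The documents do not support that. The Abstract says the study will test whether strengthening occurs, the Discussion hypothesises and suggests, and no success statement is given.
- **VSOP alone is one Discussion phrase about adaptation capacity.** The comparator is named correctly elsewhere, and if IR is not harmful, beating VSOP with IR is the stricter test. This stands, so the phrase is a minor correction.
- **Mechanism is studied.** The ANS-change and ECG analyses are reasonable supporting evidence, but they do not identify s.
- **Later trials would test the package.** Taking the package forward needs no proof of strengthening. This stands, and harm to a later trial is a possibility rather than a demonstrated consequence.

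**Conclusion.** The point holds as a mismatch between the stated objective and what the arms can estimate. RFB+VSOP against IR+VSOP gives r + s, the total effect of replacing IR with RFB when VSOP is given. The share due to strengthening is not identified: an observed 0.20 SD allows s = 0.20, s = 0 or s below zero, at any sample size. This rests on the three arms as described and on the additive mean scale of the planned models. The value v = 0.30 is only illustrative.

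Two stronger readings should be resisted. The planned contrast is not invalid: it answers whether RFB rather than IR improves outcomes alongside VSOP. Nor does the missing arm make the design indefensible. At 32 to 38 per cell, a fourth arm would have very little power for a small interaction under the assumptions shown. No arm, outcome, model or sample size is put in doubt by this point. What changes is what a positive contrast may be taken to show.

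**What to change.** 1. In the Abstract and Introduction, restate the objective as the effect of RFB rather than IR when each is given with VSOP, and fix the same wording as the permitted interpretation of RFB+VSOP against IR+VSOP.
2. In Data analysis, define additive as that total effect, so that it is not read as a test for or against interaction.
3. In the Discussion, replace VSOP alone with VSOP with IR.
4. State that a direct RFB benefit and enhancement of VSOP cannot be distinguished here, that the ANS-change and ECG analyses are supportive and associational, and that strengthening or synergy is not a conclusion the trial can support.

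Leave the hypotheses that compare the combined arm with the control groups as they are. The cost is a more modest claim and a few changed sentences, with no new arm, visit, participant or analysis.

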**Design:**

Stage II double-blinded randomized controlled trial. The study was prospectively registered at ClinicalTrials.gov, with registration approved on 21 August 2020 (No. NCT04522791).

**Setting:**

Study-related appointments will be conducted on-site at University of Rochester Medical Center locations. Data collection will be conducted from August 2020 to February 2025.

**Participants:**

Older adults with MCI (*n* = 114) will be randomly assigned to an 8-week combined intervention (RFB+VSOP), VSOP with guided imagery relaxation (IR) control, and a IR-only control, with periodical booster training sessions at follow-ups. Mechanistic and distal outcomes include ANS flexibility, measured by heart rate variability, and multiple markers of dementia progress. Data will be collected across a 14-month period.

**Discussion:**

This will be among the first RCTs to examine in older persons with MCI a novel, combined intervention targeting ANS flexibility, an important contributor to overall environmental adaptation, with an ultimate goal for slowing neurodegeneration.

**Trial registration:**

ClinicalTrials.gov NCT04522791. Registered on 21 August 2020

Protocol version: STUDY00004727; IRB protocol version 2, approved on 30 July 2020.

## Introduction

Cognitive interventions are one of two primary categories of non-pharmacological interventions that have potential for slowing the progress of dementia [1]. So far, the transferred and long-term benefits of cognitive training in groups at risk for dementia [e.g., mild cognitive impairment (MCI)], however, have been limited. Cognitive intervention theories emphasize the importance of a prolonged “mismatch” between organismic supply (e.g., a person’s brain capacity) and environmental demands (e.g., cognitive challenges) for inducing neuroplasticity. To reach an ideal “mismatch,” the complexity of an intervention needs to increase in response to performance improvement in order to constantly exceed brain capacity [2].

Older adults with MCI face ongoing challenges related to their cognitively demanding everyday activities (e.g., managing finances, remembering names, etc.) [3]. Disrupted capacity to flexibly adapt to these challenges can exacerbate poor cognitive and brain health [4]. Adaptation capacity—that is, the ability to respond flexibly to environmental demands or stressors—is a key contributor to the neuroplasticity underlying broad and sustained effects of cognitive interventions [2]. Adaptation capacity is supported by central autonomic networks [(CAN), e.g., salience network (SN), somatosensory network (SAN)], which regulate homeostatic processes including the hypothalamic-pituitary-adrenal (HPA) axis, peripheral output of the autonomic nervous system (ANS) and other metabolic systems, and behavioral responses [5]. ANS flexibility reflects the integrity of central and peripheral systems that support adaptation to environmental demands, thereby serving as a key indicator of and contributor to adaptation capacity [6]. A decline in ANS flexibility is associated with a broad range of cognitive deficits and neurodegeneration, while enhancing ANS flexibility can widely and substantially strengthen cognitive and brain function [7–10]. We suggest that adaptation capacity, by supporting responsive and adaptive changes to environmental demands, undergirds neuroplasticity. Therefore, adaptation capacity is critical for promoting neuroplasticity underlying various cognitive enhancement activities (e.g., cognitive training) [2]. Our recently completed study found that ANS flexibility at baseline predicted the training effect of a cognitive training [11]. Hence, enhancing adaptation capacity may enhance neuroplasticity and slow the progress of dementia in older adults with MCI.

There are several categories of interventions that can explicitly improve ANS flexibility, including physical exercise [12, 13], non-invasive brain stimulation [14–16], and biofeedback intervention [17]. Mechanisms underlying the improvement include modifying the central efficiency of ANS flexibility, stimulating activity of the baroreflex, or regulating dopaminergic and cholinergic transmission [15, 18]. The effect sizes of these interventions on central and peripheral pathways of ANS flexibility vary: so far, the most robust intervention effect is from HRV biofeedback intervention (HRVB). HRVB entails feeding back beat by beat heart rate data during slow breathing maneuvers such that the participant tries to maximize peripheral nervous system function (indexed by high-frequency heart rate variability (HF-HRV)). The key behavioral component of HRVB is resonance frequency (RFB), that is, breathing at a rate which maximizes respiratory sinus arrhythmia (RSA), the synchronization of HR change (increases/decreases) with respiratory (inhalation/exhalation) patterns, creating a sine-wave-like curve of peaks and valleys. Multiple mechanisms are involved in explaining the effects of RFB on ANS, including (1) phase relationships between HR oscillations and breathing at specific frequencies (i.e., maximizing RSA), (2) phase relationships between heart rate and blood pressure oscillations at specific frequencies, (3) activity of the baroreflex, and (4) resonance characteristics of the cardiovascular system, all of which have been previously reviewed comprehensively [19]. Individuals can be easily trained to engage in RFB via an assistive mobile app that guides the individual, with a visual pacer, through a paced breathing exercise. A recent meta-analysis revealed an effect size of Hedges’ *g* = 0.83 for comparing HRVB (ranges 1–50 sessions) to other control interventions on improving adaption to real-world stressors (e.g., perceived stress and anxiety trait and state) [17]. Although RFB has not been tested in groups at risk for dementia, HRVB using RFB training improves resting HRV, executive function, and anxiety in traumatic brain injury [20, 21] and older adults [22]. HRVB also improves HRV response to cognitive stress [23]. We propose that adding RFB to a cognitive training can strengthen the effect on ANS flexibility and overall adaptation capacity, which in turn may directly modify markers of dementia progression, and may also indirectly enhance individuals’ adaptation to cognitive challenges provided by the cognitive training and strengthen cognitive training effect on markers of dementia. Lastly, compared to other intervention strategies for modifying ANS flexibility (e.g., vagal nerve stimulation, exercise, non-invasive brain stimulation), we suspect our proposed intervention approach, due to the minimal side effects, self-administrable nature, and potential effectiveness, may ensure a fast translation into real-world practice.

The objective of the study is to test whether adding RFB to the vision-based speed of processing training (VSOP)—the most widely tested cognitive training among older adults [24–27]—will enhance the training effects of VSOP by strengthening adaptation capacity that affords greater adaptive learning and neuroplasticity, and slow the progress of dementia in MCI. We will examine long-term effects of the combined intervention on ANS flexibility and cognitive and functional capacity and explore potential long-term effects of the combined intervention on neurodegeneration. Relevant hypotheses include the following: the combined intervention will have a greater effect on CAN and HRV—indicators of autonomic flexibility—as well as cognition and everyday function, and less neurodegeneration, compared to control groups throughout the follow-up period; improvements in ANS flexibility will predict improvement on cognition and everyday function and slower neurodegeneration over time.

